### Data analysis

All statistical analyses will be performed on an intention-to-treat basis with alpha level set at 0.05. As suggested in an extension of the CONSORT statement for non-inferiority trial design
[45, 46], per-protocol analysis will be conducted and the results obtained by the two approaches will be compared
[47].

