### Sample size

Assuming α = 0.05, β = 0.2, and a standard deviation of 21.7 point change in SPADI scores from baseline, we estimate that 54 participants (27 per group) will be required to test for comparative efficacy between the two treatments with a non-inferiority margin of 15 points in SPADI scores. This margin is specified based on clinical judgment and is approximately two-thirds of the minimum clinically important difference of 23.1 points for the SPADI at 6 weeks
[29]. The standard deviation is obtained by adding 25% to the reported standard deviation for the change in SPADI scores at 6 weeks from baseline in a previous study comparing the responsiveness for SPADI and several indices in patients with shoulder pain receiving corticosteroid injection
[42]. The power calculation is conservative in the sense that it ignores the added power inherent in the repeated measures design (assuming a first-order autoregressive covariance structure with a within-subject correlation coefficient of 0.5, the same sample size will have an increased power of above 90% using a generalised estimating equation (GEE) approach
[43] for testing the difference in changes in scores between groups with two repeated follow-up measurements
[44]). However, it is appropriate when treatment comparisons at the two individual time points (6 weeks and 12 weeks) are performed to assess the interaction treatment effect at different time after the injection. Allowing for a drop-out rate of 15%, we will recruit a total of 64 participants (32 per group) for injection. We anticipate this will require us to assess approximately 256 participants in total, because we estimate that 25% of participants assessed will be randomised for injection. This estimate is based on a study in which an orthopaedic surgeon sent 38% of patients for subacromial injection
[8]. We anticipate some practitioner disagreement will bring the final figure to approximately 25%.

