#### Clinical efficacy

For continuous outcomes, normality of data will be assessed and parametric tests applied if normality is upheld. Treatments from the two clinicians will be compared over time (pre- to post-intervention) on an intention-to-treat basis using the GEE
[43] with a first-order autoregressive working correlation structure to account for within-subject correlation for repeated measurements. Robust estimator for covariance matrix will be adopted. The effects of time (within-group differences), practitioner (between-group differences), and practitioner by time interaction (between-group differences over time) will be included in all models and assessed using the Wald chi-square test. Non-inferiority of injection by physiotherapist to injection by surgeon will be declared if the upper limit of the one-sided confidence interval for the difference in mean change of SPADI in the physiotherapist group relative to the surgeon group is smaller than the non-inferiority margin of 15 points. Model fit and assumptions will be checked where appropriate within the GEE framework. The GEE approach works well with missing observations on outcome measures provided that they are missing completely at random
[49], which will be tested using likelihood ratio statistics
[50]. If the validity of the missing completely at random assumption was violated, adjustment using weighted GEE
[51] will be performed. Appropriate *post hoc* tests will be conducted if significant main or interaction effects are identified from the omnibus analyses
[52].

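### The non-inferiority rule reads naturally as resting on the intention-to-treat result, and the per-protocol analysis has no stated part in the claim

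*Protocol article*

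**What the plan says.** The Data analysis section of the protocol article opens with the analysis set: "All statistical analyses will be performed on an intention-to-treat basis with alpha level set at 0.05". It then cites the CONSORT extension for non-inferiority trials and says that "per-protocol analysis will be conducted and the results obtained by the two approaches will be compared". The Abstract describes the two analyses in the same way.

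Under Clinical efficacy, the two clinicians' treatments are compared by a GEE, again on an ITT basis. The declaration rule comes a few sentences later: "Non-inferiority of injection by physiotherapist to injection by surgeon will be declared" if the upper limit of a one-sided confidence interval for the difference in mean SPADI change is below 15. That sentence names no analysis set and no confidence level. Nowhere does the article require the per-protocol limit to be below 15, or say what is concluded if the two analyses disagree.

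**The concern.** In a superiority trial, deviations that make the arms more alike work against the claim, so ITT is the cautious choice. In a non-inferiority trial they work for it. If some patients allocated to the physiotherapist were injected by the surgeon, the ITT difference would shrink towards zero, and a real deficit at the margin would pass more often than the nominal error rate allows. The per-protocol analysis is the usual check on this, but here it is compared with ITT and given no stated consequence. To take an invented case, an ITT limit of 14 with a per-protocol limit of 17 would satisfy the rule as written. The investigators would then have to decide, after seeing the data, how much weight the second result carries.

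**Working it through.** **Inputs (Sample size section).** "Assuming α = 0.05, β = 0.2, and a standard deviation of 21.7 point change in SPADI scores from baseline"; a design "with a non-inferiority margin of 15 points in SPADI scores"; "we estimate that 54 participants (27 per group) will be required"; "Allowing for a drop-out rate of 15%, we will recruit a total of 64 participants (32 per group) for injection". The share of deviators, f, is an assumption, because the article gives none.

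**1. Reproduce the plan's figure.**
- Normal approximation: n per group = 2 × 21.7² × (1.645 + 0.842)² / 15² = 25.9, so 26.
- Noncentral t at one-sided 0.05: 27 per group (54 in total), power 80.6%, which matches the plan.
- One-sided 0.025 gives 33 (normal) or 34 (t) per group and does not match. The design level is therefore one-sided 0.05, that is, a one-sided 95% limit.
- Drop-out: 54 / 0.85 = 63.5, so 64, as stated.

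The point does not rest on a sample-size error.

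**2. False-claim rate if the rule uses ITT.** Take a true deficit of exactly 15 points, and let a share f of the physiotherapist arm deviate so that their deficit vanishes. The ITT difference is then d = 15(1 − f), and

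SE = 21.7 × √(2/27) = 5.906

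P(claim) = Φ((15 − d)/SE − 1.645).

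| f | d | (15 − d)/SE | False claim, 27 per arm | False claim, 32 per arm |
|---|---|---|---|---|
| 0 | 15.00 | 0 | 5.0% | 5.0% |
| 5% | 14.25 | 0.127 | 6.5% | 6.6% |
| 10% | 13.50 | 0.254 | 8.2% | 8.6% |
| 15% | 12.75 | 0.381 | 10.3% | 10.9% |
| 20% | 12.00 | 0.508 | 12.8% | 13.7% |

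The third column is for 27 per arm.

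**3. If both limits must be below 15.** This was simulated with 100,000 runs per setting, known SD, and deviators in the physiotherapist arm only, left out of the per-protocol set at random with respect to outcome. With 27 per arm, the false-claim rate under the joint rule stayed between 4.8% and 5.1% for f from 0 to 20%.

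**4. What the joint rule costs.** Simulated power at a true difference of zero:

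| f | ITT only, 27 per arm | Both, 27 per arm | ITT only, 32 per arm | Both, 32 per arm |
|---|---|---|---|---|
| 5% | 81.5% | 79.5% | 86.9% | 85.3% |
| 10% | 81.4% | 77.9% | 86.9% | 84.0% |
| 20% | 81.3% | 74.9% | 86.9% | 81.5% |

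At 10% deviation the loss is 81.4 − 77.9 = 3.5 points with 27 per arm and 86.9 − 84.0 = 2.9 points with 32. Deviation in both arms would cost somewhat more: with 24.3 per arm left (27 × 0.9), the per-protocol test by itself has 77.8% power, and the joint rule less.

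**The case against.** The strongest reply is that the rule never says ITT alone. The declaration sentence names no analysis set, a per-protocol analysis is promised because this is a non-inferiority trial, and a discordant result would be visible to readers. On this view, what remains is an unstated discordance rule, which a condensed article may leave to a fuller document. Part of this stands: that ITT decides alone is inferred from the position of the rule and from the opening sentence of Data analysis. But the article does give a complete condition for the claim, and that condition gives the per-protocol result no part. The missing definition of the per-protocol set is a different matter. It may sit in a fuller document and is not counted here.

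A second reply is that there is little to dilute. Both clinicians must already have said they would inject that day, the patient then goes to one of two rooms for a single injection, participants are blind to profession, and acupuncture is barred and monitored. This stands, and it limits the practical gain.

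Third, the dilution model is favourable to the concern. It fits a patient injected by the other clinician, but a patient in the physiotherapist arm who was never injected might do worse and widen the gap. A per-protocol set also gives up the protection of randomisation and can itself be biased. This stands too, and is why the remedy adds a condition to ITT and does not replace it.

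**Conclusion.** The point holds in a limited form. Read naturally, the article lets an ITT limit below 15 carry the claim whatever the per-protocol limit shows. The rise from 5% to about 8% at 10% dilution shows how the error rate would respond. It assumes one-sided 0.05, SD 21.7, 27 per arm, a true deficit exactly at the margin, and deviators whose deficit disappears entirely. That the joint rule holds the rate near 5% further assumes that deviation is unrelated to outcome.

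Three stronger readings are not supported:
- A reader might infer that this trial's error rate is 8% or more. The documents give no deviation rate, and the design suggests a low one.
- A reader might see a contradiction with the cited CONSORT extension. The article says that the extension suggests a per-protocol analysis, and it plans one; no conflict is visible in the text.
- A reader might add that the shared, discretionary physiotherapy narrows the difference between arms. It is protocol care in both arms, not a deviation, and patients who receive it stay in either analysis set, so it has no bearing on this point.

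The change is worth making because it is cheap and removes a choice that would otherwise be made after the results are known.

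**What to change.** Add to the declaration rule that non-inferiority is claimed only if the upper one-sided 95% limit is below 15 SPADI points in both the ITT and the per-protocol analysis, and that if they disagree the result is reported as non-inferiority not shown.

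Define the per-protocol set before unblinding, by delivery of the allocated injection: leave out patients who were not injected or were injected by the other clinician. Do not exclude for events driven by outcome, such as a further injection. That would remove poor responders and could flatter the arm with more failures.

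The wording costs a sentence or two. The price in power is small: about 78% with 27 per arm at 10% deviation, slightly under the planned 80%, or about 84% if all 32 per arm are evaluable. To keep 27 per-protocol patients per arm at 10% deviation and 15% drop-out would take 27 / 0.9 = 30, then 30 / 0.85 = 35.3, so 36 per arm (72 in total) against the planned 64. If deviation is as rare as the design suggests, the planned 64 should serve.

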#### Decision making

Agreement between the baseline assessment decisions from the two clinicians will be investigated using the proportion of observed agreement, the probability of chance agreement, the kappa statistics, and the Agreement Coefficient AC1
[48] with the 95% confidence intervals.

#### Clinical efficacy

For continuous outcomes, normality of data will be assessed and parametric tests applied if normality is upheld. Treatments from the two clinicians will be compared over time (pre- to post-intervention) on an intention-to-treat basis using the GEE
[43] with a first-order autoregressive working correlation structure to account for within-subject correlation for repeated measurements. Robust estimator for covariance matrix will be adopted. The effects of time (within-group differences), practitioner (between-group differences), and practitioner by time interaction (between-group differences over time) will be included in all models and assessed using the Wald chi-square test. Non-inferiority of injection by physiotherapist to injection by surgeon will be declared if the upper limit of the one-sided confidence interval for the difference in mean change of SPADI in the physiotherapist group relative to the surgeon group is smaller than the non-inferiority margin of 15 points. Model fit and assumptions will be checked where appropriate within the GEE framework. The GEE approach works well with missing observations on outcome measures provided that they are missing completely at random
[49], which will be tested using likelihood ratio statistics
[50]. If the validity of the missing completely at random assumption was violated, adjustment using weighted GEE
[51] will be performed. Appropriate *post hoc* tests will be conducted if significant main or interaction effects are identified from the omnibus analyses
[52].

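### Non-inferiority is judged on a SPADI change contrast not adjusted for baseline SPADI; this is valid, but gives up precision that the baseline score could supply at no cost

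*Protocol article*

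**What the plan says.** The Clinical efficacy section of the protocol article compares the two clinicians from before to after the intervention by GEE, with a first-order autoregressive working correlation and a robust covariance estimator. On the model terms it says: "The effects of time (within-group differences), practitioner (between-group differences), and practitioner by time interaction (between-group differences over time) will be included in all models". The decision rule compares "the upper limit of the one-sided confidence interval for the difference in mean change of SPADI" with 15 points.

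The Sample size section rests on the same quantity: "Assuming α = 0.05, β = 0.2, and a standard deviation of 21.7 point change in SPADI scores from baseline", "with a non-inferiority margin of 15 points in SPADI scores". It then remarks that repeated measures would add power, "assuming a first-order autoregressive covariance structure with a within-subject correlation coefficient of 0.5". Table 1 and the Primary outcome measure section show that SPADI is collected at baseline, 6 weeks and 12 weeks. Neither the model nor any other part of the article names baseline SPADI as a covariate.

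**The concern.** A difference in mean change subtracts the whole baseline score, as if baseline predicted follow-up with a slope of 1. When the slope is below 1, two things follow.

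- The contrast carries more baseline noise than it needs to, so the interval set against the 15-point margin is wider than necessary.
- A chance baseline difference is over-corrected. If the physiotherapist group happens to start better, its change looks worse, and the reverse also holds.

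With about 27 analysed per group, neither effect is negligible. At stake are the chance of showing non-inferiority when it is true, and how far the estimate depends on the luck of the baseline draw. Validity is not at stake.

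**Working it through.** **Inputs from the Sample size section:** SD of change 21.7, margin 15, alpha 0.05, power 0.80, 27 per group, drop-out 15%. **Assumptions:** true difference 0 and one-sided alpha 0.05 (the sidedness of alpha and the confidence level of the interval are not stated).

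**1. The plan's own figure.** n per group = 2 × [21.7 × (1.645 + 0.842)/15]² = 25.9, so 26. The noncentral-t version gives 27 (power 80.6%), as stated. One-sided 0.025 would need 33 (34 by t), so one-sided 0.05 is evidently what was used. Recruitment: 54/0.85 = 63.5, so 64, as stated.

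**2. What the GEE contrast is.** The stated model (three visits, time, practitioner, interaction, AR(1) working correlation) was fitted to simulated complete data. The interaction coefficient equalled the raw between-group difference in mean change, with a largest discrepancy of 4 × 10⁻¹⁵. With complete data, the working correlation therefore recovers no baseline information for the contrast at a given visit.

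**3. Variance.** With common variance s² and baseline-to-follow-up correlation rho:
- change score: 2s²(1 − rho)
- baseline-adjusted: s²(1 − rho²)
- ratio, adjusted to change: (1 + rho)/2, so the loss is (1 − rho)/2.

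**4. Numbers, holding the SD of change at 21.7 and n at 27.** Half-width = 1.645 × SD × √(2/27). Power = Φ(15/(SD × √(2/27)) − 1.645).

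| rho | variance loss | effective SD | half-width | power |
|---|---|---|---|---|
| unadjusted | – | 21.7 | 9.71 | 81.5% |
| 0.3 | 35% | 17.5 | 7.83 | 93.4% |
| 0.5 | 25% | 18.8 | 8.41 | 90.1% |
| 0.7 | 15% | 20.0 | 8.96 | 86.7% |
| 0.8 | 10% | 20.6 | 9.22 | 84.9% |

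At rho = 0.5 the standard error ratio is √0.75 = 0.866, a fall of about 13%. In 4,000 simulated trials of 27 per group, the 6-week variance ratio was 0.748 against 0.75 in theory.

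**5. Unequal variances.** With baseline SD equal to k times the follow-up SD, the ratio is (1 − rho²)/(k² + 1 − 2·rho·k). At rho = 0.5:
- k = 0.8: 0.75/0.84 = 0.89, a loss of about 11%
- k = 0.7: 0.75/0.79 = 0.95, a loss of about 5%
- k = 0.5: 0.75/0.75 = 1, no loss
- k = 1.2: 0.75/1.24 = 0.60, a loss of about 40%.

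The article gives neither SD.

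**6. Chance imbalance.** At rho = 0.5 with equal variances, s = 21.7, so the standard error of the baseline difference is 21.7 × √(2/27) = 5.9 points. An imbalance of one standard error shifts the change contrast by (1 − 0.5) × 5.9, about 3 points, or a fifth of the margin.

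**The case against.** The strongest reply is that nothing here is wrong. The trial is sized on the SD of change and tested on the difference in change against the same margin, so design and analysis agree. The contrast is unbiased over randomisations and the planned power is reached. The listed terms do not forbid a covariate that an unseen analysis plan may add. All of this stands, and it limits the point to one of efficiency. It does not remove the point, because the article itself states the model terms and the deciding contrast, and both are unadjusted.

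Three stronger readings are tempting, and the article does not support them.

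- **That the loss is a quarter on the plan's own correlation.** A reader might take the 0.5 as the baseline-to-follow-up correlation. The article attaches it to a comparison of changes over two follow-up assessments. Its claim of power above 90% reproduces (90.1%) if 0.5 is the correlation between two follow-up change scores, each with SD 21.7: their average has variance 0.75 × 21.7². With baseline as a third AR(1) outcome of common SD 21.7, the average-change contrast has 81.5% power (83.6% with optimal weights). The rho needed here is therefore an assumption.
- **That the loss is larger at 12 weeks.** Extending AR(1) to a baseline-to-12-week correlation of 0.25 implies a 12-week SD of change of 21.7 × √1.5 = 26.6. The article never gives that SD, and it treats its calculation as suitable at both follow-up times.
- **That a diluted practitioner main effect distorts the result.** This applies only if baseline is a level of time, which the pre-to-post wording suggests but the Sample size text leaves open. In either case non-inferiority is decided on the difference in change, not on that main effect.

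If change scores are the response instead, the contrast is still unadjusted and the conclusion is the same.

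**Conclusion.** The point holds as a worthwhile gain in efficiency, not as an error of validity or sample size. Under equal variances the unadjusted contrast gives up 10% to 35% of the variance for rho from 0.8 to 0.3, and 25% at 0.5. These percentages are on the variance scale; the reduction in standard error is roughly half as large. The size depends on a correlation and a variance ratio that the article does not clearly give, and it shrinks when the baseline SD is below the follow-up SD (about 11% at a ratio of 0.8 with rho = 0.5). The power figures also assume a true difference of zero, one-sided alpha of 0.05 and complete data on 27 per group.

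**What to change.** In the Clinical efficacy section, model the 6- and 12-week SPADI as outcomes, with baseline SPADI as a covariate plus time, practitioner and practitioner by time. Alternatively, keep all three records and constrain the baseline means to be equal across groups. Compare the adjusted between-group difference with the same 15-point margin, at the time point or points the plan uses for its decision.

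Treat the pain VAS in the same way. Range of movement is measured only just before and just after injection, so there the pre-injection value serves as the covariate for the post-injection value.

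The cost is a change of analysis wording. No data are added, and under randomisation the margin and the target difference stay the same; once baseline is a covariate, follow-up score and change score give the same treatment coefficient. Because recruitment has begun and interim analyses are planned at about one-third and two-thirds completion, the amendment should be dated and should state which interim results, if any, had been seen when it was made.

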#### Economic evaluation

A within-trial economic evaluation, adhering to current guidelines
[53], will be undertaken from the perspective of the health funder. A cost-utility ratio will be constructed using the formula: cost-utility = (Cost_i – Cost_c) /(QALY_i – QALY_c), where: QALY = quality-adjusted life years calculated by mapping the EQ-5D-5 L utility score across time and calculating the area under the curve, i = intervention group for main effect analysis, and c = control group. The time horizon for this economic evaluation will be 12 weeks. Direct costs will include labour costs of the clinician providing the injection, post-injection physiotherapy and change in medicine usage. Univariate, multivariate and probabilistic sensitivity analyses will be conducted to confirm stability of results and adjust for uncertainty in clinical and economic data.

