### Outcome measures

Outcomes will be measured at baseline, and at 6 and 12 weeks follow-up by the blinded assessor. These time points were chosen on the basis of a previous study evaluating subacromial corticosteroid injection that found greater improvements in the injection group at 6 weeks than at 12 weeks
[27]. At baseline the demographic, service, economic disease burden and clinical data will be recorded, including age, gender, duration of condition, imaging findings, dominant arm, affected side, medicines, occupation, shoulder-related direct and indirect costs, and usual service waiting time for care. Outcome measures and time points are displayed in Table 
1.

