#### Health-related quality of life

The European Quality of Life (five dimensions, five levels; EQ-5D-5 L) will allow quality of life to be expressed as utility values varying from 0 to 1, with 1 representing perfect health. This widely used scale builds upon the earlier EQ-5D-3 L
[34] version.

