## Discussion

The findings of this study will provide further evidence informing policy makers, regulators, health professionals, and the public as to the feasibility and safety of appropriately trained physiotherapists in Australia in requesting prescribing and administering medicines. The model of care to be evaluated in this study has the potential to reduce waiting times and improve access to appropriate and expedited care for patients who presently face long orthopaedic waiting times for specialist orthopaedic services. We anticipate this will have subsequent effects in improving patient flow, which could ultimately benefit both surgical and non-surgical orthopaedic pathways. The results may also have application for the management of other musculoskeletal presentations.

A non-inferiority randomised controlled trial design was chosen as it is appropriate when comparing an alternative treatment with an established proven effective treatment for a condition, and it is hypothesised that the alternative will not be superior in efficacy to the established treatment. In this case the objective is to determine whether the alternative treatment (physiotherapist injection) is not inferior to the existing gold standard (orthopaedic surgeon injection). This is done by assessing whether the alternative treatment falls within the non-inferiority margin
[54].

This study will be limited by its involvement of only one injecting physiotherapist. This is necessary because there is presently no regulatory framework, recognised training curriculum or accreditation process for Australian physiotherapists to prescribe or administer medicines by injection. The physiotherapist in this study obtained governance approvals on the basis of their overseas training and is not representative of other physiotherapists in Australia. If physiotherapist-led prescribing and injecting were to be implemented on a wider scale, appropriate training and regulatory frameworks would be required.

Further potential limitations of the study include differences in practice recency and frequency between the surgeon and the physiotherapist, as governance approvals permit the physiotherapist to inject only within the trial. In contrast the surgeon has recent practice and will have regular ongoing injection practice through their work outside of the research.

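### The cost-utility result is a ratio of unadjusted arm differences as printed: baseline utility makes up a quarter of each QALY with no stated adjustment, and the QALY denominator may well lie close to zero

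*Protocol article*

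**What the plan says.** In the protocol article, under Economic evaluation, the QALY is obtained by "mapping the EQ-5D-5 L utility score across time and calculating the area under the curve". The summary is fixed in the same place: "A cost-utility ratio will be constructed using the formula", which is then printed as the intervention-minus-control difference in cost over the same difference in QALYs. On the horizon the section says: "The time horizon for this economic evaluation will be 12 weeks".

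The utility times come from Outcome measures ("Outcomes will be measured at baseline, and at 6 and 12 weeks follow-up by the blinded assessor") and from Table 1, which lists EQ-5D-5L at weeks 0, 6 and 12. The section on health-related quality of life describes "quality of life to be expressed as utility values varying from 0 to 1, with 1 representing perfect health".

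The Economic evaluation section also promises to follow guidelines, which are cited but not reproduced. It plans univariate, multivariate and probabilistic sensitivity analyses to check stability and deal with uncertainty. It mentions no adjustment for baseline utility, no net-benefit measure and no acceptability curve, and it rules none of these out.

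On the expected effect, the Discussion says of the physiotherapist's injection that "it is hypothesised that the alternative will not be superior in efficacy to the established treatment". No QALY difference is given anywhere.

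**The concern.** There are two separate weaknesses, and they meet in the denominator of the printed formula.

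First, an area under the curve that starts at week 0 contains a stretch governed by utility before treatment, and later utilities are correlated with that starting value. A simple difference between arms therefore carries any chance baseline imbalance. It is also less precise than a difference adjusted for a baseline value that the trial already collects.

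Second, a trial planned on similar effect in both arms may well produce a QALY difference close to zero. Dividing by such a quantity gives a ratio that swings widely. Its sign is also ambiguous: a negative ratio means either cheaper and better or dearer and worse.

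At stake is how clearly policy makers can read the cost-utility result. The SPADI non-inferiority conclusion does not depend on it.

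**Working it through.** **The plan's own figure.** The article gives a sample size for SPADI but none for QALYs. With SD 21.7, margin 15, one-sided alpha 0.05, power 80% and a true difference of 0, the normal approximation is 2 × (1.645 + 0.842)² × 21.7² / 15² = 25.9, so 26 per arm. The t-based calculation gives 27 per arm with 80.6% power. Then 54 / 0.85 = 63.5, so 64. Both stated figures (54 and 64) reproduce, and they do so on a true SPADI difference of 0. At 27 per arm, power would be 75.6% for a true deficit of 1 point and 70.1% for 2 points. The trial is therefore sized on equal effect on SPADI. Equal utility is an inference from that.

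**Weight of baseline.** By the trapezoid rule, with times in weeks and the result in years:

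QALY = (3·u0 + 6·u6 + 3·u12) / 52

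The share of baseline is 3 / 12 = 25%. The largest possible QALY is 12 / 52 = 0.231. A baseline utility gap of 0.05 adds 0.05 × 3 / 52 = 0.0029 QALY directly, or 0.05 × 12 / 52 = 0.0115 if it persists to week 12.

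**Precision.** Assumptions, none of them given for utility in the article: SD 0.10 to 0.20, the same at each time; correlation 0.5, either first-order autoregressive (the structure the article assumes for SPADI) or exchangeable; 27 per arm. With w = (3, 6, 3) / 52 and correlation matrix R:

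- SE unadjusted = SD × √(2 · w′Rw / 27)
- Autoregressive: w′Rw = (54 + 2 × (9 + 2.25 + 9)) / 52² = 94.5 / 2704
- Exchangeable: w′Rw = (54 + 2 × (9 + 4.5 + 9)) / 52² = 99 / 2704
- Slope of QALY on baseline utility: (3 + 3 + 0.75) / 52 = 0.130 autoregressive; (3 + 3 + 1.5) / 52 = 0.144 exchangeable
- Share of variance removed by adjustment: 6.75² / 94.5 = 48%; 7.5² / 99 = 57%

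| Utility SD | Correlation | SE unadjusted | SE adjusted | Shift from a one-SE baseline imbalance |
|---|---|---|---|---|
| 0.10 | autoregressive | 0.0051 | 0.0037 | 0.0035 |
| 0.10 | exchangeable | 0.0052 | 0.0034 | 0.0039 |
| 0.20 | autoregressive | 0.0102 | 0.0073 | 0.0071 |
| 0.20 | exchangeable | 0.0104 | 0.0068 | 0.0079 |

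The last column is slope × SD × √(2 / 27); for example 0.144 × 0.0544 = 0.0079. It is √0.48 = 0.69 to √0.57 = 0.75 of the unadjusted SE. With all 32 per arm observed, the unadjusted autoregressive SEs are 0.0047 and 0.0093, so the picture is the same.

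**Sign of the denominator.** This needs no cost inputs. If the true QALY difference is 0, the estimate is negative half the time, adjusted or not. If it is 0.005 (assumed), the chance of the wrong sign is Φ(−0.005 / SE). For the autoregressive case this is 31% unadjusted and 25% adjusted at SD 0.20, and 16% and 9% at SD 0.10.

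**Spread of the ratio, for illustration only.** Cost inputs are assumed: a difference of −50 with SE 20. With 32 per arm, SD 0.20, autoregressive correlation 0.5 and a true QALY difference of 0, the simulated central 95% range of the ratio is about −84,000 to +86,000 per QALY unadjusted and −118,000 to +121,000 adjusted. Adjustment tightens the denominator around zero and so widens the ratio. It cures the first weakness and not the second.

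**The case against.** The case on the other side has real substance.

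- **Adjustment is unstated, not excluded.** The text defines how a QALY is computed, not how the arms are modelled. The article is condensed, and the full plan may name covariates. A reader might infer that the plan has decided against adjustment; the document does not support that. What stands is narrower: the formula that is printed is a ratio of simple arm differences, and a better estimator is available from data already collected.
- **Uncertainty is addressed.** The planned probabilistic analysis could produce the joint distribution of cost and QALY differences. Dominant and dominated results could then be told apart, and net benefit derived. A reader might infer that a chance imbalance or a random sign will decide the economic conclusion; that goes too far. Even so, these analyses are not a stated baseline adjustment, and the only summary named is the ratio.
- **A near-zero QALY difference is not stated.** The Discussion says only that superiority is not hypothesised. The sample size, which reproduces on a true SPADI difference of 0, makes the inference reasonable without making it a documented figure.
- **Imbalance is chance.** Under randomisation it costs precision and biases the result conditionally on the imbalance that occurred. It is not systematic bias.
- **The aim is secondary.** The Background puts economic feasibility in the overall aim but lists the comparison of costs among the secondary aims, so the cost-utility result should not be read as a main endpoint.
- **A ratio with probabilistic sensitivity analysis is common practice.** That is so. The point is an improvement to the summary, not the correction of an error in arithmetic.

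**Conclusion.** The point holds as an inexpensive improvement to a secondary economic analysis. Baseline utility carries 25% of each QALY; this follows from the article's own time points and rests on no assumption beyond straight lines between measurements. No baseline adjustment is stated. Adjustment would remove roughly half the variance of the QALY difference (48% to 57%), given the assumed correlation of 0.5. The SE of about 0.005 to 0.010 also depends on the assumed utility SD of 0.10 to 0.20.

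The instability of the ratio depends on the true QALY difference being small relative to that SE. This is plausible from the design but inferred. The wide ranges shown for the ratio depend on assumed costs and should not be quoted as properties of this trial.

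**What to change.** Amend the Economic evaluation text in four places:

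1. Estimate the QALY difference by regression of QALY on arm, with baseline EQ-5D-5L utility as covariate.
2. Report the cost difference and the adjusted QALY difference separately, each with an interval.
3. Use the probabilistic analysis already planned to present incremental net monetary benefit, λ × (adjusted QALY difference) − (cost difference), and an acceptability curve over a stated range of willingness to pay λ. This quantity involves no division, so its interval and sign stay interpretable when the QALY difference is near zero.
4. Keep the ratio as a supplementary figure, reported together with the signs of its two parts.

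The cost is analysis wording and a little more analysis, with no new data, since baseline EQ-5D-5L is already collected. The one downside is that a willingness-to-pay range must be named.
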